### Data analyses

We will accept a significance level of 5% (*p* < 0.05) corrected for multiple comparisons when needed. To assess our primary endpoint criterion, i.e., performance changes on the SA task, outcomes at baseline and at the 2-week time point will be compared using two-way analysis of variance with “time” (baseline, 2 weeks post-stimulation) and “group” (anodal, cathodal, sham) as factors. Since two comparisons will be made (sham versus left-anodal and sham versus right-cathodal tDCS) Dunnett’s two-tailed *t* test will be used to handle multiple comparisons. In the case that the data do not meet the normal distribution assumption, the non-parametric Mann-Whitney test will be used to compare performance improvements between the sham versus left-anodal and between the sham versus right-cathodal groups.

To assess the time course of potential improvements and test if such differ between the treatment groups, linear mixed models will be used with “time” (the four time points), “group” (anodal, cathodal and sham) and group-by-time interactions as fixed effects. The Benjamini and Hochberg method will be used for controlling for false discovery rate.

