### Sample size

The primary evaluation criterion is the change over 2 weeks in performance on the SA task. Performance is measured by the percentage of correct responses. The trial will be considered as positive if performances after left-anodal or right-cathodal tDCS are shown to be significantly superior to sham stimulation. The sample size is based on the results of a preliminary study comparing sham stimulation to left-anodal and right-cathodal stimulation in 12 patients [45]. In our pre-therapeutic study, the mean difference in performance improvement between sham and both anodal and cathodal stimulation was about 15% with a standard deviation of 16% and an effect size of 1.464. The difference in mean change between sham stimulation and each of the two other groups is then expected to be 15% of correct responses. The inclusion of 20 patients in each group will provide statistical power of 80%.

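### The primary ANOVA does not name the change contrast that Dunnett's test should address, and it leaves the baseline SA score unused as a covariate

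*Protocol article*

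**What the plan says.** The Sample size section of the protocol article defines the endpoint: "The primary evaluation criterion is the change over 2 weeks in performance on the SA task", measured as percent correct. It expects a 15-point difference in mean change between sham and each active arm, with an SD of 16. It claims 80% power with 20 patients per group. The trial counts as positive if either active arm is significantly better than sham.

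The Data analyses section gives the primary method: "outcomes at baseline and at the 2-week time point will be compared using two-way analysis of variance". The two factors are time (two levels) and group (three levels). Because "two comparisons will be made (sham versus left-anodal and sham versus right-cathodal tDCS"), a Dunnett "two-tailed *t* test will be used to handle multiple comparisons". If normality fails, a Mann-Whitney test is used "to compare performance improvements between the sham versus left-anodal and between the sham versus right-cathodal groups".

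The next paragraph of the same section describes a secondary linear mixed model over all four time points. That model does list "group-by-time interactions as fixed effects".

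**The concern.** In a time-by-group layout, the difference between arms in change is the interaction contrast, and its proper error is within-patient. The primary model names two factors and a multiple-comparison procedure. It does not name the interaction or a patient term, and it does not say which means Dunnett compares. The interaction is named only for the secondary model. An analyst following the sentence could therefore choose among contrasts with very different operating characteristics.

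The second issue is efficiency. Every patient is to be tested on the SA task at baseline, yet the plan does not use that score as a covariate. A pure change-score comparison is valid in a randomized trial. With 20 per arm, though, it carries any chance baseline imbalance into the estimate through regression to the mean, and it has more residual variance than a baseline-adjusted comparison.

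**Working it through.** **Inputs from the protocol article.** From Sample size: difference in mean change 15 points, SD 16 points, 20 per arm, stated power 80%. From Data analyses: two-sided 5%, Dunnett, two comparisons with sham.

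**Assumed.** The correlation r between baseline and 2-week scores is not given, so a range is shown. Score variance is taken as equal at both times.

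**Step 1: the plan's own figure.** The standard error of a difference in mean change is 16 × √(2/20) = 5.06, so the noncentrality is 15/5.06 = 2.96. An unadjusted two-sided 5% t test has 82.4% power at 20 per arm and 80.3% at 19. A simulated unadjusted Mann-Whitney test has 80.2%. The stated 80% is therefore consistent with a calculation that makes no multiplicity correction.

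**Step 2: the intended analysis, Dunnett on change.** With 57 degrees of freedom the two-sided critical value is 2.268. Against a noncentrality of 2.96:
- Each comparison: 75.5%.
- At least one arm, both effects 15 points: 88.0%.
- Both arms: 63.0%.

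For a single comparison, 22 per arm would give 79.9% and 23 would give 81.9%.

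**Step 3: baseline-adjusted analysis.** If the change SD is 16, the SD at one time point is σ = 16/√(2(1−r)). The ANCOVA residual SD is σ√(1−r²), which simplifies to 16√((1+r)/2). Noncentrality is 15/(residual SD × √(2/20)), with 56 degrees of freedom.

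| r | Residual SD | Noncentrality | Power per comparison |
|---|---|---|---|
| 0.5 | 13.86 | 3.42 | 87.3% |
| 0.7 | 14.75 | 3.22 | 82.5% |
| 0.8 | 15.18 | 3.12 | 80.2% |
| 0.9 | 15.59 | 3.04 | 77.8% |

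Power equals 80% at r ≈ 0.81. Even at r = 0.95 it is 76.6%, still slightly above the 75.5% for change scores.

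**Step 4: illustration of why the contrast must be named.** These are not the power of the planned analysis.
- Dunnett on the group main effect averages the two times. The target falls to 15/2 = 7.5 points, with SD σ√((1+r)/2). Power is 30%, 16% and 11% for r = 0.5, 0.7 and 0.8.
- The interaction contrast with repeated scores treated as independent has simulated power of about 42%, 14% and 3% for the same r.

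**Step 5: sensitivity to the SD.** The stated difference and SD give 15/16 = 0.94, not the effect size of 1.464 in the same section. An effect size of 1.464 would need an SD of 15/1.464 = 10.2. With 1.464, Dunnett on change has about 99% power per comparison. The figures in Steps 1 to 4 use SD 16.

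**The case against.** The strongest reply is that the intent is plain. The Data analyses section introduces the ANOVA as assessing changes in performance. The Mann-Whitney fallback compares improvements between the same pairs of arms. The Sample size section defines the criterion, and powers the trial, on change. A journal article also condenses the full protocol, so error terms and exact contrasts may be set out elsewhere. A change-score comparison is unbiased over randomizations, which makes ANCOVA a gain in precision and not the repair of an invalid test. Most of this stands.

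Three stronger readings are tempting, and the documents do not support them:
- A reader might infer that Dunnett will be run on the group main effect, or that the pairing will be ignored. The text says neither, so the low figures in Step 4 describe possible misreadings.
- A reader might infer that the trial falls short of its 80%. That holds only per comparison and with SD 16. Under the article's own either-arm rule, with both effects at 15 points, Dunnett on change already gives about 88%.
- A reader might infer that baseline adjustment guarantees 80% per comparison. It does so only if r is at most about 0.81. Very high r is hard to square with a change SD of 16: r = 0.9 implies a cross-sectional SD of 35.8 points on a two-choice test, where chance to ceiling spans 50 points. Still, r is unknown.

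What remains is that the article does state a primary model, that the model leaves out the term carrying the endpoint while naming it for a secondary analysis, and that a better analysis is available from data already being collected.

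**Conclusion.** The point holds as a free improvement. The primary analysis is loosely fixed: the change contrast has to be inferred from surrounding text, and the baseline score is not used for adjustment. On the intended reading, baseline adjustment moves per-comparison power from about 76% to between 87% (r = 0.5) and 78% (r = 0.9), and it removes the effect of chance baseline imbalance on the estimate. These sizes rest on an effect of 15 points, a change SD of 16, equal variances at the two times, complete data on 20 patients per arm, and an assumed r. The conflict between SD 16 and the effect size of 1.464 means that the absolute power figures could be too low. It does not affect the case for naming the contrast or adjusting for baseline.

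**What to change.** Restate the primary analysis as an ANCOVA: 2-week SA percent correct as outcome, arm as a three-level factor, baseline SA percent correct as covariate. Apply two-sided Dunnett comparisons of each active arm against sham to the adjusted means, and report both differences with simultaneous 95% confidence intervals. If the two-way layout is kept instead, state that Dunnett is applied to the group-by-time contrasts with within-patient error.

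Restate power for the chosen test, giving the correlation assumed, saying whether the 80% refers to each comparison or to the either-arm rule, and reconciling the SD with the stated effect size.

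The cost is a few sentences in the protocol or SAP before unblinding. No extra patients, visits or measurements are needed.

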## Methods

### Study design

The *STIM-SD* protocol is a double-blind, sham-controlled, randomized study testing the efficiency of periodical tDCS sessions for 10 days (Monday to Friday for 2 weeks) using language/semantic assessments, and PET and MRI-based neuroimaging at four time points: baseline and 3 days, 2 weeks and 4 months after the end of the tDCS sessions (Fig. 1a, b, and Additional file 1). The patient population (*n* = 60) is randomly assigned to three subgroups each receiving a different treatment over the ATL: left-anodal tDCS (*n* = 20), right-cathodal tDCS (*n* = 20) and sham tDCS (*n* = 20).

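### A step-down Dunnett test for the two sham comparisons would raise per-arm and both-arm power at the same 5% family-wise error, while the chance of a positive trial stays the same

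*Protocol article*

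**What the plan says.** The Data analyses section sets the overall level ("We will accept a significance level of 5" percent, corrected for multiple comparisons where needed). For the primary endpoint, the change in semantic association (SA) performance from baseline to 2 weeks, it fixes the method: "Since two comparisons will be made (sham versus left-anodal and sham versus right-cathodal tDCS) Dunnett’s two-tailed" t test. It does not mention a step-down version. If normality fails, Mann-Whitney tests replace the parametric comparisons.

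The Sample size section plans for equal benefit in both active arms: "The difference in mean change between sham stimulation and each of the two other groups is then expected to be 15% of correct responses". It reports that the pilot difference "was about 15% with a standard deviation of 16% and an effect size of 1.464". It concludes: "The inclusion of 20 patients in each group will provide statistical power of 80" percent. It does not say whether this is power for each arm or for at least one arm, nor whether Dunnett's correction entered the calculation. The trial counts as positive if either active arm is significantly better than sham.

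**The concern.** Single-step Dunnett compares both statistics with the same adjusted critical value. Once one arm has beaten sham at that value, the closed-testing principle allows the other comparison to be made at the ordinary two-sided 5% value without loss of strong family-wise control. The single-step test gives this up.

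The patients affected are those in the arm with the weaker observed result. If its statistic lies between the unadjusted and the Dunnett critical values, and the other arm is significant, single-step Dunnett reports that it did not beat sham, although an equally strict procedure would have declared it. The planning assumption is that both arms work, so this outcome is not remote.

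**Working it through.** **Inputs.** From the Sample size section: difference in mean change 15 points in each active arm, SD 16 points, 20 patients per arm, stated power 80%. From the Data analyses section: two-sided 5%, Dunnett, two comparisons. From Study design: the sample "is randomly assigned to three subgroups each receiving a different treatment over the ATL", 20 in each. Assumptions: normal data, common variance, and all 60 patients evaluable.

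**Set-up.** Each statistic is t = (active mean − sham mean) / (s × √(2/20)), with s pooled over three arms, so df = 60 − 3 = 57. The two statistics share the sham arm and have correlation 0.5. Noncentrality = (15/16) × √(20/2) = 0.9375 × 3.162 = 2.96. Critical values at 57 df: Dunnett 2.268, unadjusted 2.002.

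**The plan's own figure.** Per-arm power from the noncentral t distribution, 20 per arm:

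| Test of one arm against sham | Power |
|---|---|
| Unadjusted 5%, t with 38 df | 82.4% |
| Unadjusted 5%, Mann-Whitney (simulated) | 80.3% |
| Single-step Dunnett, 57 df | 75.5% |
| Bonferroni 2.5%, t with 57 df | 74.5% |

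Read as per-arm power, the stated 80% fits an unadjusted test and not the Dunnett test. With Dunnett, 22 per arm gives 79.9% and 23 per arm 81.9%. Read as power for at least one arm, the Dunnett test gives 88.0%, above the stated figure.

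**Single-step against step-down.** Step-down compares the larger |t| with 2.268 and, if that is significant, the other with 2.002. Simulation of 2 million trials, 15 points in both arms, SD 16, 20 per arm:

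| Power | Single-step | Step-down |
|---|---|---|
| Each arm | 75.5% | 80.1% |
| Both arms | 62.9% | 72.2% |
| At least one arm | 88.0% | 88.0% |

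The rows agree with each other. With equal effects, per-arm power is the mean of the last two rows: (88.0 + 62.9)/2 = 75.5 and (88.0 + 72.2)/2 = 80.1. The last row cannot change, because the first step is the same test.

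**Error control under step-down.** With both arms null, the family-wise error is 5.0%. With one null arm, it is rejected in 4.3% of trials when the other arm's effect is 15 points and in 5.0% when it is 30.

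**Other scenarios, SD 16.**

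- One arm 15 points, the other null: power for the effective arm 75.6% against 75.7%.
- Effects of 15 and 10 points: the weaker arm rises from 39.1% to 47.4%, and both-arm power from 35.6% to 45.4%.
- 18 evaluable per arm (an assumption, as the section gives no dropout allowance): per arm 70.3% against 75.2%; both arms 56.5% against 66.3%.

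**Sensitivity to the effect size.** 15/16 = 0.94, not 1.464. An effect size of 1.464 with a 15-point difference would imply an SD of 15/1.464 = 10.2. At 1.464 per-arm power is 99.0% single-step and 99.5% step-down.

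**The case against.** The strongest reply is that nothing in the plan is invalid. Dunnett's test suits two comparisons with a shared control and holds the 5% level. That stands: the point is efficiency, not error control. The article does not use the term single-step either. But it names the method for the primary comparisons, and the plain name denotes the single-step test.

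The second reply is that the declared success rule gains nothing. That also stands, and it limits the point to per-arm and both-arm conclusions.

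The third concerns cost. If single-step Dunnett intervals are still reported, the second arm can be significant while its interval includes zero. Under the planning assumptions this happens in 72.2 − 62.9 = 9.3% of trials, so it is a visible discrepancy that the report must handle.

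Three stronger readings are tempting, and the documents do not support them:

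- A reader might infer that the plan promises 80% per arm and misses it. The Sample size section does not say which power is meant, and under the either-arm rule in the same section the named test exceeds 80%.
- A reader might infer that equal 15-point effects are where single-step loses most. They are not: with 15 and 10 points the weaker arm loses 8.3 points (47.4 − 39.1) and both-arm power 9.8 (45.4 − 35.6), against 4.6 and 9.3 with equal 15-point effects.
- A reader might infer that the change helps to identify the more efficient modality. That aim, in Study design, is a comparison of the two active arms with each other, and a different threshold for the second sham comparison does not rank them.

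**Conclusion.** The named test is valid but less powerful than a standard alternative with the same error control. Under the plan's 15-point difference in both arms, SD 16 and 20 evaluable patients per arm, step-down Dunnett adds about 4.6 points of per-arm power and about 9 points of power to confirm both arms. The probability of a positive trial does not change.

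The gain depends on two assumptions. Both arms must have some effect; with only one effective arm it is 0.1 point. And the SD must be near 16: the 1.464 in the same section conflicts with 15/16, and if it were the true standardised difference, the per-arm gain would be about half a point. SD 16 is the reading that puts power near the stated 80%. The change is a worthwhile, inexpensive improvement and not the correction of an error.

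**What to change.** In the Data analyses section, before unblinding, replace the Dunnett sentence with wording such as: *The two comparisons with sham are tested by the two-sided step-down Dunnett procedure at a family-wise level of 5%. The larger absolute statistic is compared with the Dunnett critical value (about 2.27 at 57 df). If it is significant, the other is compared with the unadjusted two-sided 5% t value (about 2.00).*

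Add that, if single-step Dunnett intervals are reported, the step-down test decides significance, and that the second arm's interval may include zero although its test is significant.

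The cost is these sentences and the loss of exact agreement between interval and test for the second arm. No patients are added. The change covers the parametric analysis only; the Mann-Whitney fallback is not affected by it.

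### The normality-triggered fallback replaces Dunnett with two Mann-Whitney tests and names no correction, although success needs only one active arm to beat sham

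*Protocol article*

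**What the plan says.** The Protocol article, Data analyses, sets a 5% significance level "corrected for multiple comparisons when needed". The primary outcome is the change on the semantic association (SA) task from baseline to 2 weeks, analysed by a two-way analysis of variance with time and group. For the two comparisons with sham, "Dunnett’s two-tailed *t* test will be used to handle multiple comparisons".

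The next sentence replaces that test if normality fails: "In the case that the data do not meet the normal distribution assumption, the non-parametric Mann-Whitney test will be used to compare performance improvements". The contrasts stay the same, each active arm against sham, and no correction is attached to them. The paragraph on the time course then names Benjamini-Hochberg for the mixed models.

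Under Sample size, the decision rule is: "The trial will be considered as positive if performances after left-anodal or right-cathodal tDCS are shown to be significantly superior to sham stimulation". Study design gives 20 patients per arm.

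**The concern.** With two chances to succeed against one shared sham arm, the 5% level holds only if the pair of tests is corrected. The article does this by name for the parametric route. It then lets the trial's own data replace that route with one that has no named correction, and Dunnett's t test does not carry over to two Mann-Whitney tests.

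The general promise to correct when needed does not say how. On the least favourable reading, failing a normality check would make success easier: each comparison would be judged at 5%, whereas Dunnett judges each at about 2.7%. The decision at stake is the trial's main claim, that at least one form of stimulation is superior to sham.

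**Working it through.** **Inputs.** Two comparisons, two-sided 5%, Dunnett on the main route, Mann-Whitney on the fallback (Data analyses). Success if either arm is superior; difference 15 points, SD 16, 20 per group, 80% power (Sample size). Allocation 20:20:20 (Study design).

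**1. The plan's own figures.** n per group = 2(z₁₋α/₂ + z₀.₈)²(16/15)².
- α = 0.05: 2 × (1.960 + 0.842)² × 1.138 = 17.9, so 18.
- α = 0.025: 2 × (2.241 + 0.842)² × 1.138 = 21.6, so 22.

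The stated 20 lies between the two. Dunnett with three arms of 20 (57 df) has a simulated critical value of 2.27, which is a per-comparison level of 2.7% and 5% for the pair.

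**2. Correlation of the two contrasts.** They share the sham mean. With equal arms the correlation is (σ²/20)/(2σ²/20) = 0.5.

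**3. Family-wise error if the fallback is unadjusted.** Let Z₁ and Z₂ be standard normal with correlation 0.5.
- Either direction: 1 − P(|Z₁| < 1.96, |Z₂| < 1.96) = 1 − 0.909 = 9.1%.
- False superiority only: 1 − P(Z₁ < 1.96, Z₂ < 1.96) = 1 − 0.955 = 4.5%, against the nominal 2.5% for one direction.
- Upper reference, independent tests: 1 − 0.95² = 9.75%.
- Simulated Mann-Whitney tests, 20 per arm: 9.1% with the exact critical value; 8.2% to 8.8% with the continuity-corrected test on normal, skewed and 26-item discrete data.

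**4. With a correction.** Under Holm or Bonferroni the first rejection needs p < 0.025. Family-wise error is then 4.6% (bivariate normal) or 4.1% to 4.3% (simulated).

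**5. The whole rule, switch included.** The documents give neither a score distribution nor a normality criterion, so both are assumed here: no treatment effect, binomial change scores, patients who differ in ability, and Shapiro-Wilk at 5% as the trigger. The rule uses Dunnett unless the check fails, and unadjusted Mann-Whitney tests otherwise.

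| Assumed mean accuracy | Switch occurs | Error of the whole rule |
|---|---|---|
| 70% to 80% | 7% to 17% of trials | 5.5% to 6.7% across both of these rows |
| 88% | 31% to 38% | (as above) |
| Near ceiling | 64% | 8.1% |

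The first two rows use 26 or 52 items and a between-patient SD of 10 to 12 points. Dunnett kept throughout stayed at 4.4% to 5.1%, near the ceiling included.

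A further run checked the analysis recommended below (2-week score adjusted for baseline, Dunnett-type critical value of 2.27). It used 26 items, mean accuracy of 70, 80, 88 and 93%, between-patient SD of 12, 12, 10 and 7 points, and 8,000 null trials each. Error was 4.5% to 5.1%.

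**6. Power at a difference of 15 and SD 16, normal data.** Mann-Whitney per comparison: 79.7% at 0.05 and 69% at 0.025. At least one arm significant at 0.025, if both arms have the effect: 84%. Dunnett per comparison: 75.6%.

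**The case against.** The strongest reply is that the article does not say the fallback is uncorrected. Its opening sentence promises correction when needed, and two tests under an either-arm rule are plainly such a case. An analysis plan, not shown here, may name the method, and a condensed article may leave that to it. This stands in part: a missing name alone would be a small point. But the article itself fixes the data-driven change of primary test, and that change removes the one correction it names for these comparisons.

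A reader might infer more than the text supports:

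- **That the success rule runs at about 9%.** That figure applies only if the general promise is ignored and only in trials that reach the fallback. It also counts false findings in both directions.
- **That the fallback loses baseline adjustment.** It does not. With two time points, the time-by-group contrast in the analysis of variance compares changes, as the Mann-Whitney tests do. Neither adjusts for baseline as a covariate.
- **That the endpoint will probably trigger the switch.** The documents give no score distribution. The bounded quantity is the raw score, whereas the fallback compares changes. The SA task also has a verbal and a picture form of 26 trials each, so a score out of 26 holds per form.
- **That no correction is possible for rank tests.** Holm and rank-based many-to-one tests both serve.
- **That the primary test is left open.** The switch, the replacement test and its contrasts are all stated. Only the criterion for non-normality is not, and that may sit in the analysis plan.

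**Conclusion.** The concern holds in a limited form. The plan moves its primary test, on a data-driven trigger, from a procedure with a named correction to two tests with none named, under a rule that needs only one of them to succeed. If the tests are left unadjusted, two-sided family-wise error is about 9% in trials using the fallback, and false superiority is about 4.5% against 2.5%. These two figures rest only on the equal allocation, the shared sham arm and the 5% level. For the whole rule the error is roughly 5.5% to 7%, and about 8% in the scenario closest to the ceiling. Those figures also depend on assumed score distributions and an assumed normality check.

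In the same scenarios Dunnett without the switch held about 5%, so the switch is not needed to protect the error rate. The point should be corrected, but it does not undermine the design.

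**What to change.** Remove the normality-triggered switch and fix one primary analysis in advance: the 2-week SA score by group, adjusted for baseline SA score, with Dunnett for the two contrasts with sham. Baseline SA is already collected, so this adds no data. Keep Mann-Whitney on the change scores as a sensitivity analysis, with Holm across the two comparisons.

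If the fallback is kept as a primary route, state in the same sentence that Holm or a rank-based many-to-one test applies to it.

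The cost is a wording change. An adjusted Mann-Whitney test loses some power: per comparison it falls from 79.7% at 0.05 to 69% at Holm's first threshold of 0.025, under the planned difference and SD. Dunnett on the main route already carries a similar price. With strongly skewed changes a rank test could be the more powerful choice, which is a reason to keep it as the sensitivity analysis. The Trial status section reports 13 patients randomised by March 2019 and recruitment expected to end in June 2021, so on that timetable the change could be made well before the final analysis.

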The primary endpoint of the *STIM-SD* protocol is to evaluate the potential therapeutic efficacy of multiday tDCS (10 days) on language/semantic performance in patients with SD (see the section “Language/semantic tasks” – the semantic association task). In addition, we will also (1) assess the time course of potential language/semantic improvement through the application of four follow-up time points; (2) assess neuroimaging biomarkers (PET and MRI) that could reflect stimulation-induced neuroplasticity and response to stimulation; (3) compare the effects of left-anodal and right-cathodal tDCS to define the most efficient stimulation modality; (4) identify biomarkers that could individually predict tDCS impact and (5) improve the understanding of the semantic roles of the left and right ATL and their potential structural connectivity, contributing to the definition of anatomic-functional models of semantics.

The protocol has been approved by the local Ethics Committee and is registered in ClinicalTrials.gov with the identifier NCT03481933 and the study title “‘Evaluation of a Transcranial Stimulation with Direct Current on Language Disorders in Semantic Dementia (STIM-SD)”*.* Written informed consent is obtained from all patients and healthy subjects before the onset of any of the study procedures. All research protocol visits take place at the same site, the Pitié-Salpêtrière Hospital. Two additional centers contribute to the protocol by recruiting patients with SD.

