To identify imaging bio-markers of stimulation-induced neuroplasticity, we will analyze cortical metabolism and resting-state functional connectivity. PET images will be used for cortical metabolism, to analyze tissue metabolic activity and regional glucose uptake in the brain. A voxel-based analysis, using the Statistical Parametric Mapping (SPM) software [66], will be implemented to highlight regional differences in metabolism between the images obtained at baseline and post-stimulation. The resting-state fMRI sequence will be explored to study the status of functional connectivity within the language/semantic networks and possible alterations within it between baseline and post-stimulation images. Quantification of functional connectivity will be based on integration measures in specific networks established from the known anatomy, on indices derived from the graph theory or information theory. Cortical regions of interest will be obtained automatically using SPM toolboxes. More specifically, the language/semantic network will include the middle and anterior portions of the lateral ATL, the inferior frontal gyrus, the dorsomedial and ventromedial prefrontal cortex and the inferior parietal lobe. To study the neurophysiological impact of tDCS on specific brain networks, resting-state EEG datasets obtained at baseline and 3 days after the end of the 10 tDCS sessions will be also analyzed. Data will be filtered (4–40 Hz) and power distribution and local synchrony calculated across frequency bands and compared. Functional connectivity maps across the electrodes will be estimated by calculating the phase-lockimg value between the eight EEG leads and have them compared across in pairs.

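### PET and resting-state fMRI change is stated only as baseline versus post-stimulation, so as written the search for stimulation-induced change has no contrast with sham

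*Protocol article*

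**What the plan says.** Under Methods, Study design, one of the additional aims is to "assess neuroimaging biomarkers (PET and MRI) that could reflect stimulation-induced neuroplasticity and response to stimulation". The Data analyses section turns this into an analysis: "To identify imaging bio-markers of stimulation-induced neuroplasticity, we will analyze cortical metabolism and resting-state functional connectivity".

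The contrasts follow in the same paragraph. For FDG-PET, a voxel-based SPM analysis "will be implemented to highlight regional differences in metabolism between the images obtained at baseline and post-stimulation". For resting-state fMRI, connectivity in the language and semantic network is to be studied, together with "possible alterations within it between baseline and post-stimulation images". Neither sentence mentions group, sham or an interaction. For EEG, recordings from baseline and from 3 days after the last session are to be analysed and compared, but the terms of the comparison are not given.

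Earlier in the section the language outcomes are handled differently. For the semantic association (SA) task, group is a factor and each active arm is set against sham: "Since two comparisons will be made (sham versus left-anodal and sham versus right-cathodal tDCS) Dunnett’s two-tailed *t* test will be used". For the time course, the mixed model has time, then "group” (anodal, cathodal and sham) and group-by-time interactions as fixed effects".

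**The concern.** The imaging aim is causal: change brought about by stimulation. A baseline versus post-stimulation difference estimates the stimulation effect plus everything else that moves between the two scans. In this trial that includes repeat-scan effects, scanner drift, regression to the mean and some progression of a neurodegenerative disease. A randomised sham arm on the same scan schedule exists to remove these, yet the stated imaging contrasts do not use it.

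If the analysis is run as worded, a shift shared by all three arms could be reported as a marker of tDCS-driven plasticity. The mechanistic conclusion would then rest on an uncontrolled comparison inside a sham-controlled trial.

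**Working it through.** **Is a sham contrast for imaging change stated anywhere?**

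- Data analyses, SA task: group is a factor, with each active arm against sham.
- Data analyses, time course: group (including sham) and group-by-time.
- Data analyses, PET and resting-state fMRI: the two time points only.
- Data analyses, EEG: comparison not defined.
- Data analyses, structural and diffusion MRI: responders against non-responders, which is not a comparison with sham.
- Study design: healthy participants are assessed once, so they cannot show change between scans.

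Sham is therefore the only source of information on between-scan change without active stimulation, and no stated imaging analysis uses it. The scans straddle a 2-week course and a further 2 weeks (Study design; PET-MRI neuroimaging), so they are about 2 + 2 = 4 weeks apart or more.

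**Inputs.** There are 20 patients per arm (Sample size) and the significance level is 5% (Data analyses). The article gives no SD, effect size or power for PET or fMRI, so there is no stated figure to reproduce. Let *s* be the SD of the change score for one regional measure. Let *k* be a mean change shared by all arms, in units of *s*. Values of *k* are assumptions.

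**Step 1: rejection probability of a pre/post test when tDCS has no effect.** A two-sided paired t test on *n* patients has noncentrality *k*√*n* on *n* − 1 degrees of freedom. Its chance of rejecting is:

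| *k* | one arm, n = 20 | both active arms, n = 40 | all patients, n = 60 |
|---|---|---|---|
| 0 | 5% | 5% | 5% |
| 0.1 | 7% | 10% | 12% |
| 0.2 | 14% | 24% | 33% |
| 0.3 | 25% | 46% | 63% |
| 0.5 | 57% | 87% | 97% |

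Three sample sizes are shown because the article does not say whether arms are pooled. For change in an active arm minus change in sham, the expected difference is *k* − *k* = 0, so the rejection probability is 5% for every *k*. These figures are for a single test. A stricter threshold over voxels makes rejection rarer but leaves the shared shift in the estimate.

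**Step 2: what the controlled contrast costs.**

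- Within one arm: SE = *s*/√20 = 0.224 *s*.
- Active minus sham: SE = *s*√(2/20) = 0.316 *s*.
- Ratio = √2 = 1.41.

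With 20 per arm (noncentral t, 38 df, two-sided 5%, unadjusted), the controlled contrast has power of 34% for a true difference of 0.5 *s*, 69% for 0.8 *s* and 80% for about 0.91 *s*. Correction over voxels or connections would lower these.

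**The case against.** The strongest reply is that silence is being read as a decision. This is a journal article; the full protocol and analysis plan are not shown, and the second-level design of a secondary imaging analysis is often left to them. A difference between baseline and post-stimulation could also describe the change score that is then compared between arms. The Study design section presents imaging within one sham-controlled randomised trial, and the imaging aims are worded as exploratory.

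Part of this stands. A reader might infer that the authors have chosen to leave sham out; the text does not say so, and nothing in it excludes a group term. Four further inferences also go beyond the document:

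- **That EEG is a pre/post analysis.** The comparison is undefined, not stated as pre/post.
- **That the 30 to 40 minute start of PET acquisition biases the result.** The same window applies at both visits in all arms. Without a systematic shift between visits it adds noise, not direction.
- **That regions significant in an active arm but not in sham will be taken as evidence.** No such procedure is proposed.
- **That multiplicity is ignored.** Data analyses opens with a general provision for correction.

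What does not stand is the claim that only detail is missing. The section states a contrast for PET and fMRI, that contrast does not match the causal aim, and the same section names group and the interaction where language outcomes are concerned.

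**Conclusion.** The point holds as a mismatch between aim and stated contrast. For PET and resting-state fMRI the article states only baseline versus post-stimulation; for EEG it leaves the comparison open. If analysed as written, change common to all arms could be read as an effect of tDCS.

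The size of the bias cannot be derived from the document. The rejection probabilities above depend wholly on the assumed shared drift, and progression over about four weeks may be small. Repeat-scan effects, scanner drift and regression to the mean do not need a long interval. The protection offered by the sham contrast assumes that such changes are alike across the randomised arms.

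The consequence is confined to the secondary, mechanistic claims. Trial success is defined on the SA task against sham, and that conclusion is unaffected. This should be corrected, but it does not threaten the primary result.

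**What to change.** State in the Data analyses section that:

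- the inferential test for PET and resting-state fMRI change, and for EEG change, is group-by-time: change in each active arm minus change in sham;
- this test falls under the multiplicity correction that the section already announces;
- within-arm baseline versus post-stimulation maps are descriptive;
- the term stimulation-induced is reserved for the group-by-time result.

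No new data or scans are needed, because sham patients follow the same imaging and EEG schedule; only the contrast in the models changes. The cost is precision: the standard error is about 1.41 times that of a within-arm test with 20 per arm, so moderate imaging effects may be missed.
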